##### **Adequate clinical and parasitological response**

- absence of parasitaemia on day 28 (day 42), irrespective of axillary temperature, in patients who did not previously meet any of the criteria of early treatment failure, late clinical failure or late parasitological failure

*P. vivax* infections that recur after drug treatment can have 1 of 3 etiologies: 1) recrudescence, 2) reinfection, or 3) relapse arising from the dormant liver stage (hypnozoites). In order to differentiate the recurrent parasitemias as identical vs. different from the original infection, a genotypic analysis will be performed by PCR including characterizing microsatellite markers to assess recrudescence from reinfection and for drug resistance markers. Molecular testing for gametocytes will also be conducted on any smear positive days. Those who fail in the chloroquine arm will have CQ levels tested from the already collected filter paper. Lumefantrine level on day 7 will be measured for those receiving AL treatment from collected filter papers. Patients noted to have G6PD deficiency by the fluorescent spot test and those with hemoglobin drop of >2.4g/dL will undergo additional G6PD genotyping.

**Valid end-points** include treatment failure, completion of the follow-up period without treatment failure, loss to follow-up, withdrawal from study (voluntary or involuntary, and protocol violation). Loss to follow-up occurs when, despite all reasonable effort, an enrolled patient who does not attend the scheduled visits, cannot be found. Patients who withdraw from the study during the treatment period (days 0-2) will be treated with CQ according to the national policy. They will be referred back to the clinic to continue with care.

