#### **Criteria for withdrawal/protocol violation**

Patients meeting any of the following criteria will be withdrawn:

- Withdrawal of consent
- Failure to complete the treatment
- Vomiting both initial and replacement doses at any single time in the treatment (i.e. If the patient vomits both attempts to administer the morning dose that would require withdrawal; however, vomiting the initial morning dose but not the morning replacement dose would not require withdrawal), persistent vomiting
- Severe side-effects necessitating hospitalization
- Progression to severe malaria
- Occurrence during the follow-up of concomitant disease that would interfere with a clear classification of the treatment outcome
- Antimalarial (or antibiotics with antimalarial activity) treatment administered by a third party or self-medication with antimalarial (or antibiotics with antimalarial activity- Annex IV) assessed by asking participants or their caretaker at follow-up visits
- Erroneous inclusion of a patient outside of the inclusion/exclusion criteria
- Misclassification of a patient due to a laboratory error (parasitemia) leading to the administration of the rescue treatment

Patients who are withdrawn will be followed up if possible and will be censored or excluded from the analysis. The reasons for discontinuation or protocol violation will be recorded on the case report form.

**Training for personnel:** Clinicians and laboratory personnel are trained and licensed in Ethiopia. In addition, they will receive approximately 1 week additional training to review the protocol of this study. In addition to technical aspects of specific laboratory techniques and clinical assessments, training will stress the importance of confidentiality, and appropriate techniques for obtaining informed consent. Continued appropriate processes with regard to informed consent will be reinforced by intermittent observation by the supervisor. The staff will include 1-2 laboratory technicians for microscopy, and 1-2 staff persons for enrollment and clinical assessments.

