## EMERGENCY CARE

Any patient with treatment failure or recrudescence will receive quinine 10mg/kg/dose every 8 hours for 7 days. This will be given orally unless the patient has persistent vomiting, in which case the patient will be referred to the nearest hospital to receive IM/IV therapy.

Patients with signs of severe malaria (altered mental status, coma, convulsions, hemoglobin <5g/dl, respiratory distress, circulatory collapse, or abnormal bleeding), persistent vomiting or severe side effects will be hospitalized and receive parenteral therapy with artesunate (or quinine if not available) and relevant supportive treatments, according to National Guidelines.

Any participant who develops urticaria or difficulty breathing following administration of the treatment drug will be treated with diphenhydramine or chlorpheniramine and will be withdrawn from the study. In addition, patient and or their parents, caretakers and family members will be counseled that the patient should not receive additional doses of the antimalarial they were given. These patients will be treated with oral quinine for seven days as per the rescue protocol.

Adult patients and parents with children in the study will be encouraged to return to the clinic for any fever or other signs of illness on any day during the follow-up period, allowing for early detection and treatment of illness before it becomes severe. Any hospitalization which occurs during the follow-up period will be paid for by the study.

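### The rule giving chloroquine to patients who withdraw on days 0-2 conflicts, read literally, with the emergency-care rules for drug reactions and severe cases, and the protocol states no precedence

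*Protocol*

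**What the plan says.** Four places in the protocol bear on what a patient receives after leaving treatment early.

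- **END-POINTS, the Valid end-points paragraph** (at the end of Adequate clinical and parasitological response). It lists "withdrawal from study (voluntary or involuntary, and protocol violation" among the valid end-points. Shortly afterwards it says: "Patients who withdraw from the study during the treatment period (days 0-2) will be treated with CQ according to the national policy". It adds that these patients go back to the clinic for further care.
- **Criteria for withdrawal/protocol violation**, which follows directly. Its reasons include withdrawal of consent, "Severe side-effects necessitating hospitalization", progression to severe malaria, and persistent vomiting.
- **EMERGENCY CARE.** On drug reactions: "Any participant who develops urticaria or difficulty breathing following administration of the treatment drug will be treated with diphenhydramine or chlorpheniramine and will be withdrawn". The patient and family are "counseled that the patient should not receive additional doses of the antimalarial they were given", and the follow-on treatment is seven days of oral quinine. For the severe group, which includes severe malaria, the rule is that those with "persistent vomiting or severe side effects will be hospitalized and receive parenteral therapy with artesunate" (quinine if artesunate is unavailable).
- **METHODS TO MINIMIZE RISKS.** This repeats the reaction rule as far as antihistamine and withdrawal. Its counselling then concerns other antimalarials, with a pointer to Annex IV, and it names no follow-on drug.

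**The concern.** The chloroquine (CQ) sentence is general: it depends only on withdrawal within a time window. The emergency rules depend on the reason for withdrawal. Where a patient satisfies both, staff hold two instructions naming different treatments.

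The overlap matters most in the CQ arms. A patient who reacts to CQ is withdrawn. One section then gives CQ, while another says "the patient should not receive additional doses of the antimalarial they were given. These patients will be treated with oral quinine". The stake is re-exposure to the suspected drug at the moment of a reaction. For severe cases in any arm, the stake is uncertainty between CQ and hospital treatment. This is a patient-safety matter and does not bear on the trial's inference.

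**Working it through.** The plan has no figure to reproduce here. The check sets the sections side by side.

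**1. Can a reaction to CQ fall inside the window?** Yes. Laboratory Evaluations gives the first dose of artemether-lumefantrine (AL) or CQ on day 0, and Annex V schedules AL or CQ on days 0, 1 and 2. The window in the CQ sentence is the same three days.

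**2. Does the CQ sentence reach patients whom the study team removes?** On its wording it can. Its paragraph counts involuntary withdrawal and protocol violation as withdrawal. The next section lists clinical reasons alongside withdrawal of consent. Nothing confines the CQ sentence to consent.

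**3. What does each section instruct for the same patient?**

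| Patient withdrawn on days 0-2 | END-POINTS sentence, read literally | EMERGENCY CARE | Can both be followed? |
|---|---|---|---|
| CQ or CQ+PQ arm, urticaria or breathing difficulty | CQ | Counselled against more of the drug given; oral quinine | No; CQ would be the suspected drug |
| AL or AL+PQ arm, same reaction | CQ | Counselled against more of the drug given; oral quinine | No; the follow-on drugs differ, but CQ is not a repeat of AL |
| Any arm, severe malaria, persistent vomiting or severe side effects | CQ | Hospital, parenteral artesunate (or quinine) | No |
| Any arm, consent withdrawn, no clinical event | CQ | Not addressed | No conflict |

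**4. Does any section give precedence?** No. END-POINTS and EMERGENCY CARE do not refer to each other. END-POINTS cites national policy, and EMERGENCY CARE cites national guidelines for severe cases, so that appeal does not rank them. METHODS TO MINIMIZE RISKS does not help either: its counselling concerns other antimalarials, and the Annex IV list it points to contains both chloroquine and quinine. The section on identifying and managing adverse events separately treats breathing difficulty as a severe reaction to be referred to the district hospital.

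**5. Does it reach the analysis?** No. Withdrawn patients are censored or excluded (Criteria for withdrawal/protocol violation). The data analysis plan drops them from the per protocol analysis and counts them in the survival analysis only up to the day before drop-out. Treatment given after withdrawal therefore does not enter the efficacy estimates, and the sample-size calculation does not use it.

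**The case against.** The best counter-argument is that the conflict disappears on a sensible reading. The CQ sentence speaks of patients who withdraw, in the active voice, whereas the withdrawal criteria and EMERGENCY CARE speak of patients who will be withdrawn. Sending patients back to the clinic suits someone leaving the study better than someone sent to hospital. The words on involuntary withdrawal belong to a list of end-points and do not define the scope of the treatment sentence. EMERGENCY CARE is also the more specific rule and covers a reaction from antihistamine to follow-on drug, so staff using it would not re-dose with CQ.

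This is a fair reading and may be the intended one. It lowers the likelihood of harm. It does not remove the conflict, because the protocol neither limits the sentence to voluntary withdrawal nor says that the specific rule prevails.

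Several stronger readings are not supported:

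- **That the protocol orders CQ for everyone who leaves early, while elsewhere forbidding it.** The sentence is unqualified but does not say all, and EMERGENCY CARE speaks of counselling, not prohibition.
- **That half the trial is affected.** With 120 patients per treatment, 2 × 120 = 240 of 4 × 120 = 480 are planned for the CQ arms. That is the number allocated, not the number who would react on days 0-2. The protocol gives no rate, and known hypersensitivity is an exclusion criterion.
- **That the sentence doubles the CQ dose.** Drug Dosing and Regimens gives 10, 10 and 5 mg base/kg, a total of 25. If treatment with CQ meant completing the course, the total would stay at 25 mg base/kg. If it meant a new full course after one, two or three doses, the totals would be 10 + 25 = 35, 20 + 25 = 45 or 25 + 25 = 50. The protocol does not say which is meant, so the finding is an unstated rule with a range of 25 to 50, not an overdose.
- **That every vomiting withdrawal is in conflict.** The criterion "Vomiting both initial and replacement doses at any single time in the treatment" is listed separately from persistent vomiting, and only persistent vomiting triggers the hospital rule.

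**Conclusion.** The point stands as an internal contradiction in clinical management. Read literally, a CQ-arm patient who reacts on days 0-2, and a patient in any arm withdrawn then for severe malaria, persistent vomiting or severe side effects, come under incompatible instructions with no stated precedence. This rests on one assumption: that the CQ sentence covers involuntary as well as voluntary withdrawal, which its paragraph permits and nothing excludes. If only voluntary withdrawal was meant, the defect is that the protocol does not say so.

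The number of patients cannot be derived from the protocol and is probably small. The point merits correction because the ambiguity would arise during a drug reaction or severe illness and is easily removed.

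**What to change.** The sponsor's clinical team should reconcile the Valid end-points paragraph, Criteria for withdrawal/protocol violation, EMERGENCY CARE and METHODS TO MINIMIZE RISKS, so that each withdrawn patient falls under one instruction. The amended text should state:

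1. which withdrawals the CQ sentence covers, by reason and by arm;
2. how it applies to a patient who has already received CQ;
3. one version of the reaction rule, used wherever it appears. The hospital referral for breathing difficulty in the adverse-event section should be checked at the same time.

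Which treatment applies in each case is for the clinical team, and none is proposed here. The cost is a short wording amendment and a mention in the staff training already planned. It needs no extra patients, visits or procedures and no change to the analysis.

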#### **Criteria for withdrawal/protocol violation**

Patients meeting any of the following criteria will be withdrawn:

- Withdrawal of consent
- Failure to complete the treatment
- Vomiting both initial and replacement doses at any single time in the treatment (i.e. If the patient vomits both attempts to administer the morning dose that would require withdrawal; however, vomiting the initial morning dose but not the morning replacement dose would not require withdrawal), persistent vomiting
- Severe side-effects necessitating hospitalization
- Progression to severe malaria
- Occurrence during the follow-up of concomitant disease that would interfere with a clear classification of the treatment outcome
- Antimalarial (or antibiotics with antimalarial activity) treatment administered by a third party or self-medication with antimalarial (or antibiotics with antimalarial activity- Annex IV) assessed by asking participants or their caretaker at follow-up visits
- Erroneous inclusion of a patient outside of the inclusion/exclusion criteria
- Misclassification of a patient due to a laboratory error (parasitemia) leading to the administration of the rescue treatment

Patients who are withdrawn will be followed up if possible and will be censored or excluded from the analysis. The reasons for discontinuation or protocol violation will be recorded on the case report form.

**Training for personnel:** Clinicians and laboratory personnel are trained and licensed in Ethiopia. In addition, they will receive approximately 1 week additional training to review the protocol of this study. In addition to technical aspects of specific laboratory techniques and clinical assessments, training will stress the importance of confidentiality, and appropriate techniques for obtaining informed consent. Continued appropriate processes with regard to informed consent will be reinforced by intermittent observation by the supervisor. The staff will include 1-2 laboratory technicians for microscopy, and 1-2 staff persons for enrollment and clinical assessments.

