#### Phase2:

- 1) **Efficacy:** To measure the clinical and parasitological efficacy of AL vs. AL+PQ, or CQ vs. CQ+PQ among patients  $\geq 12$  months of age suffering from uncomplicated vivax malaria by determining the number of recurrent vivax episodes (symptomatic as well asymptomatic) in patients receiving PQ versus patients who don't receive PQ during a 12 month follow up period.

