## DATA HANDLING AND ANALYSIS

### **Data analysis plan, including statistical methodology and planned tables and figures**

SAS 9.3 (Cary, NC) as well as the WHO drug efficacy tools provided at <http://www.who.int/malaria/toolsformonitoring.html> will be used for data management and analysis. Data will be analyzed using two methods: **per protocol analysis**, where patients who were withdrawn from the study or who were lost to follow-up are excluded, and **survival analysis**, where all enrolled patients are included in the analysis until the last day before drop-out. In addition to voluntary withdrawals or treatment non-compliance, patients will be considered for the analysis as withdrawn if the PCR results are unclassifiable.

The final analysis will include:

- A description of the patients screened, and the distribution of the reasons for exclusion.
- A description of the patients included in the study.
- The proportion of patients lost to follow-up or withdrawn and the distribution of reasons for withdrawal.
- The proportion of treatment failures in each Pv arm at day 28 and day 42 with 95% confidence intervals using both methods of analysis.
- Frequency of side effects, severe malaria, anemia, and hospitalizations by treatment arm.
- Comparison in absolute means and relative changes in hemoglobin concentration during follow-up after treatment
- Comparison of number of recurrent parasitological vivax episodes after initial parasite episode.

**Data collection:** Data will be collected and recorded at the health facility by one of the trained staff members. All data entry forms will be checked for completeness. Laboratorians may complete brief reports on laboratory findings to share with clinicians who will transfer these results to the case report form of the appropriate patient, the laboratory results will be entered into an Excel database.

**Information management and analysis software:** Microsoft Excel (Redmond, Washington) will be used for double entry of laboratory data and clinical data. SAS 9.3 (Cary, NC) will be used for data analysis.

**Data entry, editing, handling, storage and disposition:** Some open-ended data including the names of specific drugs or diagnoses will be coded prior to data entry. A list of standard codes for these fields will be developed by hand once collection of data is complete. All forms will then be coded and checked by 2 different team members.

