#### **ANNEX IV Drugs with antimalarial activity that should not be used during the study**

- chloroquine, amodiaquine;
- quinine, quinidine;
- mefloquine, halofantrine, lumefantrine;
- artemisinin and its derivatives (artemether, arteether, artesunate, dihydroartemisinin);
- proguanil, chlorproguanil, pyrimethamine;
- sulfadoxine, sulfalene, sulfamethoxazole, dapsone;
- primaquine;
- atovaquone;
- antibiotics: tetracycline\*, doxycycline, erythromycin, azithromycin, clindamycin, rifampicin, trimethoprim;
- pentamidine

\* Tetracycline eye ointments can be used.

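### The withdrawal rule for outside antimalarials and antibiotics has no time limit, so in the 12-month recurrence comparison removal depends on the outcome and may bias the primaquine effect, probably toward a smaller one

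*Protocol*

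**What the plan says.** In the protocol, the list under Criteria for withdrawal/protocol violation opens with "Patients meeting any of the following criteria will be withdrawn". One item is an antimalarial, or an antibiotic with antimalarial activity, given by a third party or taken through "self-medication with antimalarial (or antibiotics with antimalarial activity- Annex IV) assessed by asking participants or their caretaker at follow-up visits". Annex IV names the antibiotics, among them "doxycycline, erythromycin, azithromycin, clindamycin, rifampicin, trimethoprim". The consequence is stated once for all criteria: "Patients who are withdrawn will be followed up if possible and will be censored or excluded from the analysis". No item has a day limit, and nothing separates the 42-day Phase 1 from the 12-month Phase 2.

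The Phase 2 objective is to measure efficacy over 12 months by "determining the number of recurrent vivax episodes (symptomatic as well asymptomatic) in patients receiving PQ versus patients who don't receive PQ". Efficacy end points defines any vivax parasitaemia in the year after clearance as a recurrence, and keeps a patient whose recurrence is treated in the randomised arm until follow-up ends.

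The Data analysis plan leaves withdrawn and lost patients out of the per-protocol analysis, carries everyone to the last day before drop-out in the survival analysis, and lists among the final analyses "Comparison of number of recurrent parasitological vivax episodes after initial parasite episode".

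**The concern.** The criterion makes sense for the day-28/42 outcome, where an outside drug blurs the call between cure and failure. For a year-long count of recurrences it works differently. A patient whose recurrence is seen and treated by the study stays in. A patient with the same recurrence treated at another facility or at home is withdrawn. That episode has no study slide and is not counted, and all later ones leave the analysis too.

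Patients without PQ are expected to recur more often, so they would meet the criterion more often and sooner. Removal is then linked to the outcome and differs by arm. At stake is the Phase 2 question of how many recurrences PQ prevents in a year. The Summary makes outside treatment plausible: it says that malaria is frequently treated without laboratory confirmation and that about half of suspected cases are tested.

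**Working it through.** **The plan's own figures.** There is none for Phase 2. The group sizes under Sample size determination reproduce: 97 for 68% vs 87.2% (1 − 0.32 × 0.40) at alpha 0.05; 118 for 68% vs 87% at alpha 0.025; 68 for 58% vs 83% at alpha 0.05. All concern day 42, as does the 10–20% loss allowance, so they do not bear on this point.

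**Inputs.** The Introduction quotes cumulative relapse risks by day 157 of 61.8% for chloroquine alone and 26.3% with PQ. Taking these as constant hazards, which is an assumption:

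- no PQ: λ0 = −ln(1 − 0.618) × 365/157 = 2.24 per year
- PQ: λ1 = −ln(1 − 0.263) × 365/157 = 0.71 per year
- true ratio 0.71/2.24 = 0.32 (0.317 unrounded); true difference 2.24 − 0.71 = 1.53 episodes per patient-year

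The share q of recurrences treated outside is not in the protocol. I assume 10–40%, equal between arms, and no unrelated courses.

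**Homogeneous risk, unadjusted counts.** The withdrawal hazard is h = qλ, the proportion withdrawn by month 12 is 1 − e^(−h), mean follow-up is (1 − e^(−h))/h, and counted episodes per patient are (1 − q) × λ × mean follow-up. At q = 20% without PQ: h = 0.447, withdrawn 0.361, follow-up 0.81 year, counted 1.44. With PQ: h = 0.142, withdrawn 0.132, follow-up 0.93 year, counted 0.53.

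| q | Withdrawn, no PQ vs PQ | Counted episodes, no PQ vs PQ | Ratio | Difference |
|---|---|---|---|---|
| 10% | 20% vs 7% | 1.80 vs 0.62 | 0.34 | 1.19 |
| 20% | 36% vs 13% | 1.44 vs 0.53 | 0.37 | 0.91 |
| 40% | 59% vs 25% | 0.89 vs 0.37 | 0.42 | 0.52 |

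**What the rule adds.** If the same patients were kept in, the outside-treated episodes would still lack slides, and the count would be (1 − q)λ. The ratio would be 0.32 and the difference (1 − q) × 1.53 = 1.38, 1.22 and 0.92 at q = 10, 20 and 40%. The rule itself therefore accounts for the further fall to 1.19, 0.91 and 0.52.

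**Other estimators.** The table gives the PQ/no-PQ ratio at q = 10/20/40%. Varied risk means a gamma frailty with mean 1 and variance 1, simulated with 400,000 patients per arm.

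| Estimator | Homogeneous risk | Varied risk |
|---|---|---|
| Unadjusted count | 0.34 / 0.37 / 0.42 | 0.36 / 0.40 / 0.47 |
| Censored, per person-time | 0.32 throughout | 0.34 / 0.36 / 0.38 |
| Withdrawn patients excluded | 0.32 throughout | 0.36 / 0.40 / 0.47 |

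With equal q the absolute difference falls below 1.53 in every cell; at q = 20% it lies between 0.73 and 1.22.

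**Unrelated antibiotic courses alone.** At an assumed 0.3 per year and q = 0, 26% of both arms are withdrawn and the ratio stays at 0.32.

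**Unequal shares, varied risk.** With q of 30% without PQ and 10% with PQ, the ratio is 0.50–0.64. With 10% and 30% it is 0.25, which exaggerates PQ. In that last case withdrawal is 18% in both arms, so the shift comes from the uncounted episodes: 0.317 × 0.70/0.90 = 0.25.

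**The case against.** Several stronger readings are tempting, and the protocol does not support them.

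- *The rule ends participation.* Withdrawn patients are followed up where possible, and censoring keeps their earlier episodes. What is lost is their place in the analysis from then on, and assured scheduled slides.
- *The plan fixes a raw count.* It names the number of episodes as the outcome but does not rule out person-time. A count or rate model may properly be left to a statistical analysis plan, and a survival analysis is planned. With person-time the ratio moves little or not at all.
- *The bias is certainly toward no effect.* The trial is open label, so equal outside-treatment shares cannot be presumed, and the direction can reverse.
- *The antibiotic list adds to the bias.* If use is equal between arms, it costs follow-up and precision only.
- *Outside treatment usually means a vivax recurrence.* The protocol describes presumptively treated cases as a mixture of non-malaria, falciparum and vivax.

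The safeguards also count. There are weekly calls, a slide at every monthly visit, a study card, home tracing and free care, and recurrences without symptoms give little reason to seek treatment elsewhere. These could keep q low. The stated primary outcome, at day 28/42, is not affected.

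All of this limits the size and certainty of the point. It does not change what happens once a recurrence is treated elsewhere: withdrawal is mandatory, has no day limit, and depends on the outcome. A later analysis plan cannot recover slides that were not scheduled.

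**Conclusion.** The point holds for Phase 2 in this limited form. Applied for 12 months, the criterion makes removal from the recurrence comparison depend on the outcome, and it may bias the PQ effect. A smaller apparent effect is the likely direction, not a certain one. With equal outside-treatment shares the absolute difference shrinks under each estimator examined. The ratio attenuates for unadjusted counts, and also under censoring or exclusion when risk varies between patients.

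The size rests on an assumed q of 10–40% and on constant hazards taken from a chloroquine study and applied here as repeat-episode rates, including to the artemether-lumefantrine arms. It is an illustration, not an estimate. A reader might infer that PQ's benefit will be badly understated; the figures do not establish that, because q is unknown and person-time removes much or all of the shift in the ratio. The change is still worth making, because the rule loses information that the planned visits could collect.

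**What to change.** Limit this withdrawal criterion to the day-28/42 efficacy classification. For Phase 2, state that outside antimalarial or Annex IV antibiotic use is recorded with drug and date at the monthly visits and weekly calls, that the patient stays on scheduled follow-up, and that all slide-positive vivax episodes are analysed by randomised arm per person-time.

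Add a sensitivity analysis that counts outside antimalarial treatment for fever as an episode and removes a fixed, pre-stated window after it from time at risk. This is needed because keeping the patient in does not restore the episode that had no slide, and that loss may differ between arms.

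The cost is protocol wording and a few form fields, since the visits and calls are already planned. No treatment changes. The downside is small: some retained person-time follows an outside drug with a short suppressive effect, and the sensitivity analysis addresses it.

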**Sampling, sample size and statistical power****Sample size determination:**

The design of the study is to compare the addition of PQ to AL or CQ alone. From our previous efficacy study, CQ alone showed a success rate of 68% at day 42 (null hypothesis). It will be assumed under the alternative hypothesis that the addition of PQ will decrease the chance of relapse by at least 60% resulting in a success rate of 87%. Group sample sizes of 97 in each group will achieve 90% power to detect a difference between group proportions of 19% using the two-sided Z-test with pooled variance test statistic. The significance level of the test was targeted at 0.05. Adjusting the alpha level to 0.025 for multiple comparisons will increase the sample size to 118 in each group. The AL arm showed even a lower efficacy at day 42 in our previous study of 58%. Using this lower success rate of 58% seen with AL at day 42, resulted in a smaller required sample size of 68. Taking into account 10-20% loss to follow-up at 42 days, a sample size of 120 subjects for each treatment was determined to be optimal.

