### For artemether-lumefantrine or chloroquine:

#### **Early treatment failure**

- danger signs or severe malaria on day 1, 2 or 3 in the presence of parasitaemia;
- parasitaemia on day 2 higher than on day 0, irrespective of axillary temperature;
- parasitaemia on day 3 with axillary temperature  $\geq 37.5$  °C;
- parasitaemia on day 3  $\geq 25\%$  of count on day 0.

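### The withdrawal rule can remove or censor patients who meet a failure definition, and may remove incomplete PQ courses; no planned analysis uses later outcomes in the assigned arm

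*Protocol*

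**What the plan says.** Three parts of the protocol bear on this.

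- **Withdrawal criteria** (Criteria for withdrawal/protocol violation). Meeting any listed criterion leads to withdrawal. The list includes "Progression to severe malaria" and, separately, not completing treatment. The consequence is stated once for the whole list: "Patients who are withdrawn will be followed up if possible and will be censored or excluded from the analysis".
- **Failure definitions** (Early treatment failure, Late clinical failure, repeated in Annex I). Early failure includes "danger signs or severe malaria on day 1, 2 or 3 in the presence of parasitaemia". Late clinical failure covers the same event from day 4 to day 28 (day 42).
- **Analyses** (Data analysis plan). Two methods are named. The first is per protocol, "where patients who were withdrawn from the study or who were lost to follow-up are excluded". The second is a survival analysis that takes in everyone enrolled but follows each patient only to the day before leaving. Non-compliance with treatment is also handled as withdrawal.

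Under Drug Dosing and Regimens and Annex V, AL and CQ are three-day courses on days 0 to 2. PQ is a 14-day course starting on day 2.

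**The concern.** Severe malaria with parasitaemia is one of the clearest failures the endpoint can record. If withdrawal takes precedence, that patient leaves the per-protocol denominator, and in the survival analysis contributes event-free time up to the day before. The protocol does not prevent this reading.

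The completion rule raises a different problem. It is written for every arm, but a 14-day course gives many more chances of not completing than a 3-day course. If it covers PQ, removal after randomisation depends on the factor that was randomised. The patients who remain in the PQ arms are those who finished, and they need not have the same prognosis as the whole of the comparison arm. The survival analysis then rests on the assumption that non-completers, had they stayed, would have failed at the same rate as completers. That is doubtful for a drug whose effect depends on the course being taken.

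The Introduction frames the PQ question as current practice without PQ against a 14-day PQ regimen, to inform national policy. Patients who start PQ and do not finish belong in that answer.

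**Working it through.** **1. The protocol's own planning figures.** Inputs from Sample size determination: CQ success 68% at day 42; 60% fewer failures with PQ, so success = 1 − 0.4 × 0.32 = 0.872, stated as 87%; AL success 58%, so with PQ 1 − 0.4 × 0.42 = 0.832. The test is specified as "using the two-sided Z-test with pooled variance test statistic". Per group,

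n = [z(1−α/2)·√(2·p̄·q̄) + z(1−β)·√(p1·q1 + p2·q2)]² / (p2 − p1)².

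- 0.68 vs 0.872, α = 0.05, 90% power: n = 97, matching "Group sample sizes of 97 in each group will achieve 90% power". With the rounded 0.87, n = 100, and power at 97 is 89.3%; this is rounding only.
- 0.68 vs 0.87, α = 0.025: n = 118, as stated.
- 0.58 vs 0.83, α = 0.05: n = 68, as stated.

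The figures reproduce, and none is disputed. The planned CQ-pair gap of 19 points (19.2 unrounded) is the base for what follows.

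**2. One event, two classifications.** Take a patient with severe malaria and parasitaemia on day 3.

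- Endpoint definitions and Annex I: early treatment failure.
- Withdrawal section: withdrawn, then censored or excluded.
- Per-protocol analysis: absent if treated as withdrawn.
- Survival analysis: event-free to the day before, if treated as withdrawn.

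No sentence ranks the two classifications.

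**3. Size of the severe-malaria effect.** The protocol gives no expected count, so 1 to 3 cases per arm of 120 are assumed.

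- No PQ: 38/120 = 31.7% failures; removing 1 to 3 gives 37/119 = 31.1% to 35/117 = 29.9%.
- PQ: 16/120 = 13.3%; removing 1 to 3 gives 15/119 = 12.6% to 13/117 = 11.1%.

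The shift is about 0.6 to 2.2 points within an arm. Its effect on the comparison depends on which arm loses more cases.

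**4. Size of the PQ non-completion effect.** Assume that a fraction w of the PQ arm does not finish and fails at the no-PQ rate, while completers have the planned success rate. With everyone kept as randomised, the difference is (1 − w) × the completers' difference.

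| w (assumed) | CQ pair, planned 19.0 points | Power, 120 per arm, α = 0.025 |
|---|---|---|
| 0 | 19.0 | 90.6% |
| 5% | 0.95 × 19.0 = 18.0 | 86.6% |
| 10% | 0.90 × 19.0 = 17.1 | 81.7% |
| 20% | 0.80 × 19.0 = 15.2 | 69.4% |

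The power column assumes that all 120 per arm are analysed. On the unrounded rates, as-randomised failure in the PQ arm is 0.9 × 0.128 + 0.1 × 0.32 = 14.7%, or 0.8 × 0.128 + 0.2 × 0.32 = 16.6%, against 12.8% per protocol. For the AL pair, 25.2 points becomes 22.7 (w = 10%) or 20.2 (w = 20%).

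**5. If the withdrawn differ in prognosis.** Suppose PQ had no effect, failure was 32% in both arms, and 10% of the PQ arm with failure risk r were removed. Observed PQ failure is (0.32 − 0.1r)/0.9. For r = 0.5 it is 30.0%, a spurious benefit of 2.0 points; for r = 1 it is 24.4%, or 7.6 points. If r were below 0.32 the bias would go against PQ. The protocol gives no information on r, so this shows only how the result depends on it.

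**The case against.** The strongest reply has five parts.

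- **Failure may take precedence.** Treatment failure and withdrawal are listed as separate valid end-points, and a patient who has met a failure criterion can never be an adequate response. It is fair to read this as failing first and then leaving. A reader might infer that the worst failures are certainly counted as non-events; the text does not establish that. It leaves the matter open, and that is the defect.
- **Treatment may mean AL or CQ only.** Just before the withdrawal list, the protocol describes the treatment period as days 0 to 2, which would make the completion rule fall equally on all arms. This stands as an ambiguity. Handling non-compliance as withdrawal in the data analysis plan points the other way. Nor is completion after day 2 a PQ-only matter over the full year, because the efficacy end points section has recurrences re-treated in every arm. Supervised PQ dosing and tracing of defaulters should also keep non-completion down.
- **The survival analysis starts from everyone.** A reader might infer that neither analysis compares the randomised groups. That is too strong: all enrolled patients enter the survival analysis, and its weakness is informative censoring at withdrawal.
- **Safety is covered.** A reader might infer that withdrawal for side effects hides the worst haemolysis. The protocol does not support this. Safety end points and the data analysis plan call for adverse events, side effects, anaemia and hospitalisations by arm, and the two analysis methods are attached only to the failure proportions.
- **Per protocol plus survival analysis is a recognised efficacy approach**, and a SAP, which was not available, may add analysis sets. Both are fair, but the protocol itself fixes these two methods and itself contains the conflict over severe malaria.

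**Conclusion.** The point holds in two parts. First, the withdrawal section and the failure definitions classify severe malaria with parasitaemia in opposite ways, without a precedence rule, so true failures can be lost from the efficacy analyses. The number lost is small if such cases are rare, and the direction of any bias in the PQ comparison is not fixed: if they were commoner without PQ, losing them would shrink the apparent benefit.

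Second, if treatment in the withdrawal section includes PQ, the completion rule removes or informatively censors patients mainly in the PQ arms during initial treatment, and neither planned analysis uses what happens to them afterwards. Under an assumed 10-20% non-completion with reversion to 32% failure, the CQ-pair benefit is about 17-15 points rather than 19. That range rests on two assumptions the protocol does not supply: the non-completion rate (its own 10-20% is loss to follow-up, a different quantity) and no benefit at all from a partial course. On these figures the conclusion about PQ would not reverse; its size would be overstated.

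**What to change.** - Reconcile the withdrawal section with the failure definitions and Annex I: in every efficacy analysis, a patient who meets a failure definition counts as a failure on that date, whatever the withdrawal status. This concerns counting only and leaves clinical care unchanged.
- State whether treatment, in the completion criterion and in the non-compliance sentence of the data analysis plan, includes PQ.
- Add an analysis of all patients randomised to PQ or no PQ, in their assigned arm, using the smears available after PQ non-completion. Preferably make it the primary comparison, with per protocol as supportive. G6PD-deficient patients, who stay in the AL-alone or CQ-alone arms without being randomised to PQ or no PQ, fall outside this set.

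The cost is protocol and SAP wording. The PQ effect may come out slightly smaller. Follow-up after withdrawal is promised only where possible, so some later outcomes will be missing, and the report should say how many per arm.
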